### Data management

A data management plan has been developed using the Swedish Research Council template including plans for secure storage and data quality. All participants will receive a personal code and data will be pseudonymized. Data will be collected and managed using the electronic data capture tool REDCap [61] on secure, encrypted servers at Karolinska Institutet with access restricted to authorized study personnel. Regular backups will be performed, and an audit trail will document all data changes. Qualitative data will be recorded and transcribed verbatim, and interviews will be pseudonymized before analysis. All data will be retained for 10 years after study completion in accordance with GDPR and institutional policies, after which it will be securely destroyed. The findings will be disseminated through peer-reviewed open-access publications, presentations in the municipality and reports for stakeholders and end-users.

### Data analysis

All analyses will be performed as an intention-to-treat analysis. Descriptive statistics will be used to summarize participant characteristics at baseline per study arm. Prior to analysis, the distribution of the outcomes will be assessed for normality and homogeneity. Between arm differences for outcomes, BMI z-score (primary outcome), %IOTF-25, probability of reaching BMI z-score cut-offs and WHtR will be analyzed.

To analyse the primary outcome of BMI z-score we will fit a linear mixed model with BMI z-score at 0, 3, and 12 months as the outcome variable, including a random intercept for each child. Fixed covariates will be treatment assignment (ML or control), time (in months), their interaction, and baseline weight status. The effect of the treatment will be assessed by the interaction parameter, which is interpreted as the difference in change of BMI z-score per month” between the two randomisation arms. A dose-effect analysis will be performed to assess the effect of number of ML sessions attended. This will be performed by replacing the treatment variable in the regression model with a variable indicating how many sessions the child’s parents attended.

The register control arm will be compared against the ML arm regarding BMI z-score, %IOTF-25, probability of reaching BMI z-score cut-offs and WHtR, using the same methods as described above adjusted for confounders. Secondary outcomes will be analyzed using the same principles as above. Interviews with parents and HCP will be transcribed verbatim and analyzed using reflexive thematic analysis [73–75]. We will explore causal pathways between effectiveness- and implementation outcomes by integrating the quantitative and qualitative data. Missing data will be evaluated for its extent and patterns. If missingness in key outcomes (e.g., BMI z-score, %IOTF-25, BMI z-score cut-offs, WHtR) exceeds a predefined threshold, appropriate statistical methods such as multiple imputation will be applied. Full details about the analysis will be described in the Statistical Analysis Plan, which will be finalized and published in Clinicaltrials.gov before the end of data collection.

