### Sample size

We estimate that the trial will need 126 children (63 children in the intervention and 63 in the control group) to be able to detect a difference at 12 months between the groups in BMI z-score of -0.16 with a standard deviation of 0.3, 80% power and an alpha level of 0.05, including an estimated 10% loss to follow-up.

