### Randomization

When parents have signed the consent form, they will be randomized to a treatment arm using REDCap randomization module [61]. A block randomization with a block size of six will be used to ensure a balanced allocation across treatment arms within each stratum. Stratification into the two strata overweight and obesity will be performed based on the baseline BMI z-score. Each block of six will have three participants in the intervention arm and three in the control arm, and the order of assignments within each block will be random. To include 126 participants, 21 blocks are needed. A research assistant will inform the clinics about which arm the participant belongs to. Neither HCPs nor parents will be blinded to allocation. The statistician remains blinded to group allocation until the analyses are performed to ensure objectivity. HCPs will not have access to the random allocation sequence.

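### The primary mixed model is valid but uses the baseline BMI z-score inefficiently: the arm-by-time test is a comparison of change, and the weight-status term adds essentially no precision to it

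*Protocol article*

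**What the plan says.** All references are to the protocol article.

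- **Data analysis, outcome.** The primary analysis is a "linear mixed model with BMI z-score at 0, 3, and 12 months as the outcome variable, including a random intercept for each child".
- **Data analysis, fixed effects.** "Fixed covariates will be treatment assignment (ML or control), time (in months), their interaction, and baseline weight status". Time is in months and enters linearly. No product of weight status and time is listed.
- **Data analysis, test.** "The effect of the treatment will be assessed by the interaction parameter", read as a difference in monthly change. Secondary outcomes follow the same approach, and so does the comparison with the register controls, there with adjustment for confounders.
- **Randomization.** "Stratification into the two strata overweight and obesity will be performed based on the baseline BMI z-score". On its natural reading, the weight-status covariate is this stratum.
- **Sample size.** "We estimate that the trial will need 126 children (63 children in the intervention and 63 in the control group"), for a 12-month difference in "BMI z-score of -0.16 with a standard deviation of 0.3, 80% power and an alpha level of 0.05". The total also allows for dropout, "including an estimated 10% loss to follow-up". No credit is taken for covariate adjustment.

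**The concern.** Randomisation makes the expected baseline BMI z-score equal in the two arms. The stated model does not use this: its treatment main effect lets the arms differ freely at month 0. The arm-by-time term then rests on within-child change alone. That removes a chance baseline imbalance in level, but not the part of the later difference that arises from regression to the mean.

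Weight status does not make up for this. It is fixed within a child and enters only as a main effect, so it shifts the whole trajectory and leaves the slope alone. A reader may believe that the primary test gains precision from the stratum when it does not.

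What is at stake is precision from data that the trial already collects. The trial is sized at 80% power, and the Discussion expects difficulty in recruiting parents and keeping them in the programme.

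**Working it through.** **1. The plan's own figure.** Inputs from Sample size: difference 0.16, SD 0.3, 80% power, alpha 0.05 (taken as two-sided), 10% loss.

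n per arm = 2 × (1.960 + 0.842)² × 0.3² / 0.16² = 55.2, so 56. Then 56 / 0.9 = 62.2, so 63 per arm and 126 in total. The figure reproduces. Power of a simple two-group comparison at 56 per arm is 80.6%.

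**2. Power of the stated slope model.** Assumptions: complete data on 56 per arm, a linear effect reaching 0.16 at month 12, a random intercept with correlation rho between any two visits, and 0.3 as the SD of change.

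- SD of change 0.3 gives a residual variance of 0.09 / 2 = 0.045.
- Visits at 0, 3 and 12 have mean 5 and sum of squared deviations 25 + 4 + 49 = 78.
- Variance of 12 × slope per child = 144 × 0.045 / 78 = 0.0831.
- SE of the arm difference = √(2 × 0.0831 / 56) = 0.0545.
- Power = Φ(0.16 / 0.0545 − 1.96) = 83.6%, for any rho.

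**3. What a common baseline mean adds.** In units of the total variance, the within-child information on the slope difference is W = 78 / (1 − rho). Dropping the treatment main effect adds B = 5² / (rho + (1 − rho)/3). The variance ratio is W / (W + B). At rho 0.5, W = 156 and B = 37.5, so the ratio is 0.806.

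| rho (assumed) | Variance cut | SE cut | Power, 0.3 = SD of change | Power, 0.3 = SD of 12-month value |
|---|---|---|---|---|
| 0.5 | 19.4% | 10.2% | 83.6% → 90.5% | 83.6% → 90.5% |
| 0.7 | 10.7% | 5.5% | 83.6% → 87.5% | 96.7% → 98.0% |
| 0.8 | 6.9% | 3.5% | 83.6% → 86.1% | 99.6% → 99.8% |
| 0.9 | 3.3% | 1.7% | 83.6% → 84.8% | above 99.9% both |

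In the last column the residual variance is 0.09 × (1 − rho), so the stated model itself gains power as rho rises.

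**4. What the weight-status main effect adds.** Simulated trials of 56 per arm, 60 replicates per scenario, fitted with and without the term:

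- Complete data: the largest change in the interaction estimate was about 1e-14, and the mean SE on the 12-month scale was 0.0537 both ways.
- 10% missing at month 12: the mean SE went from 0.0566 to 0.0565, about 0.2%. Across the scenarios, the 12-month estimate moved by at most about 0.012.

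**5. What weight status × time would add.** In the same simulations with complete data, the mean model SE was unchanged when trends did not differ by stratum. It fell from 0.0545 to 0.0537 (1.6%) for an assumed 12-month difference in trend of 0.15, and from 0.0579 to 0.0544 (6.0%) for 0.30.

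**The case against.** The strongest reply is that this is a choice between valid models. The stated model has no bias in expectation and no inflated error rate. The sample size was computed without adjustment, and under linear change the slope model already exceeds it. All of that stands, and it rules out three stronger readings that a reader might infer:

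- **That the model ignores baseline and stratum.** It does not. Baseline BMI z-score is the month-0 response, so the contrast is a difference in change, and the stratum is named as a covariate. What is absent is the equal-baseline constraint and any action of the stratum on change.
- **That weight status can never alter the tested slope.** This is exact only with complete data. With the planned 10% loss it moves the result slightly.
- **That 126 is too few, or that ten points of power are lost.** The sample size is not undercut. A gain near ten points (80.6% to 90.3%) arises only in a comparison at month 12 alone, at rho 0.5. If 0.3 is the SD of change, rho 0.5 implies a visit SD of 0.3 / √(2 × 0.5) = 0.30, rho 0.8 implies 0.47 and rho 0.9 implies 0.67. The sample spans overweight and obesity, and nothing in the article supports the low end.

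Two further objections concern the remedy. First, Table 4 puts randomisation in a column before T0, where weight and height are listed; a baseline taken after unblinded allocation would not be equal by design. But allocation is stratified on baseline BMI z-score, so a value from before allocation must exist and can be used. Second, "Full details about the analysis will be described in the Statistical Analysis Plan", so detail is deferred. The article nevertheless already fixes the fixed effects and the tested parameter, and a SAP that only adds detail would carry them forward.

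**Conclusion.** The point holds as an efficiency improvement, not as an error. The stated test is a valid comparison of change that leaves some baseline information unused, and its weight-status term contributes essentially nothing to it. The cost is 3% to 19% of the variance of the tested slope for rho from 0.9 to 0.5. If 0.3 is the SD of change, that is about 1 to 7 points of power from a starting point of about 84%. If 0.3 is the SD of the 12-month value, the gain is about 1 point at rho 0.7 and negligible from 0.8.

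These figures rest on a random-intercept correlation, a linear effect, complete data on 56 per arm, and a rho that the article does not give. The article also does not settle which SD 0.3 is. The direction is not in doubt: using the baseline does not lose efficiency in expectation.

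**What to change.** State one of the following in the SAP for the randomised comparison:

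- **Common baseline mean.** Keep months 0, 3 and 12 as outcomes and drop the treatment main effect, leaving time, treatment × time and weight status.
- **Baseline as covariate.** Model the 3- and 12-month values with baseline BMI z-score as a continuous covariate, plus the stratum.

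These are alternatives, not the same model. With linear time, the first fixes the 3-month effect at one quarter (3/12) of the 12-month effect; the second need not.

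In either case, use the measurement taken before allocation. Weight status × time may be added, at the cost of one parameter; it helps only if trends differ by stratum. Use the same form for the continuous secondary outcomes, each with its own baseline. Do not impose the common baseline mean in the register comparison, which is not randomised.

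The cost is wording. No data, visits or children are added, and the article says the SAP will be final before data collection ends, so the change can still be prespecified.

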**Fig. 1 Fig1:**
[figure not shown]
The Co-Fam model

The HSS program has been provided in grade one to all children and their families attending public schools in this municipality since 2022. The program is based on Social Cognitive Theory [19] and consists of four components: (1) A parental guide with health information available in 11 languages; (2) a motivational interview with parents performed by the school nurse; (3) classroom activities for the children performed by teachers with home assignments; and (4) a T2D risk self-assessment test for parents [44]. For a detailed description of the HSS program see Elinder et al. [45]. The HSS program has been evaluated regarding implementation showing that the program can be performed with relatively high fidelity, although somewhat lower in families with a non-Nordic background mainly due to language issues when performing the motivational interview [46]. Qualitative studies with school personnel and families have shown that teachers, school nurses, parents and children overall have a positive attitude towards the program and that it has raised the health literacy of the participants in both theory and practice [47–50].

The ML parental support program is grounded in Social Learning Theory [51, 52] and Social Interaction Learning Theory [19, 51] which together emphasize how parenting practices, social interactions, and broader environmental contexts influence children’s behaviors [53]. The ML program is based on a manual and consists of ten weekly 90-minute group sessions, led by primary healthcare personnel (HCP) (dieticians and physiotherapists) trained as group leaders (Table 2). The group sessions are followed by six individual booster sessions every six weeks for another nine months. Group sessions focus on strengthening parent-child communication to achieve healthy behaviors through evidence-based parenting practices, including positive reinforcement and role modeling, with role play and peer discussions as key components for building skills. Parents receive handouts briefly outlining the content of each session, including home assignments. The booster sessions focus on the families’ individual needs and provide an opportunity to follow up on the relevant topics covered during the group sessions.

**Table 2 Tab2:** Content of the group sessions in the More and Less parental support program (month 1–3)

Session	Topic	Content overview

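### The trial is sized on a 12-month difference in BMI z-score, but the primary test is one linear slope over 0, 3 and 12 months; the two agree only if the 3-month effect is a quarter of the 12-month effect.

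*Protocol article*

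**What the plan says.** Under Sample size, 126 children (63 per arm, allowing 10% loss to follow-up) are needed "to be able to detect a difference at 12 months between the groups in BMI z-score of -0.16 with a standard deviation of 0.3", at "80% power and an alpha level of 0.05". The text does not say whether 0.3 is the SD of the 12-month value or of the change from baseline.

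Under Data analysis, the primary model is a linear mixed model for BMI z-score at 0, 3 and 12 months with a random intercept per child. "Fixed covariates will be treatment assignment (ML or control), time (in months), their interaction, and baseline weight status". The treatment effect is "assessed by the interaction parameter, which is interpreted as the difference in change of BMI z-score per month". No 12-month contrast, categorical visit or check of linearity is named.

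Under The Co-Fam model, ML starts with ten weekly 90-minute group sessions, which Table 2 places in months 1 to 3. "The group sessions are followed by six individual booster sessions every six weeks for another nine months".

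Data analysis leaves full details to a later SAP, but the form of time and the parameter that carries the treatment effect are already fixed in the protocol.

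**The concern.** With time entered in months, the model forces the arm difference to grow by the same amount every month from 0 to 12. If it does not, the interaction estimates neither the 3-month nor the 12-month difference. It estimates a weighted mix in which the 3-month effect counts with the opposite sign to the 12-month effect.

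Contact is concentrated in the first three months, so an effect that does not accrue evenly is a realistic possibility. The reported primary effect could then misstate the 12-month difference for which the trial was sized, and the test could have less power than planned. The same model is reused for the dose-effect analysis and the register comparison, and its principles extend to the secondary outcomes, so the choice reaches beyond one test.

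**Working it through.** **Inputs from the protocol.** 12-month difference -0.16, SD 0.3, 80% power, alpha 0.05, 10% loss, 63 per arm (Sample size); visits at 0, 3 and 12 months, linear time, random intercept (Data analysis). **Assumed:** two-sided alpha, complete data for the slope weights, and a range for the 3-month difference, which the protocol does not give.

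**1. The stated sample size reproduces.** n per arm = 2 × (1.960 + 0.842)² × 0.3² / 0.16² = 55.2, so 56. Dividing by 0.9 gives 62.2, so 63 per arm and 126 in total. This is a plain two-group comparison at 12 months; 56 evaluable per arm gives 80.6% power.

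**2. What the slope estimates.** With complete data, the random-intercept interaction equals the arm difference in within-child least-squares slopes. The mean time is (0 + 3 + 12)/3 = 5 and the sum of squares is 25 + 4 + 49 = 78. Writing d0, d3 and d12 for the arm differences at each visit:

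12 × slope = 12 × (-5·d0 - 2·d3 + 7·d12)/78 = -0.769·d0 - 0.308·d3 + 1.077·d12.

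Randomisation makes d0 zero in expectation. Setting 1.077·d12 - 0.308·d3 = d12 gives d3 = d12/4, which is the linear path.

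**3. Results across trajectories.** Power is for the slope test with 56 per arm, taking 0.3 as the SD of the 12-month change. The residual SD is then 0.3/√2 = 0.212, the SD of 12 × slope is 12 × 0.212/√78 = 0.288, and its SE is 0.288 × √(2/56) = 0.0545.

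| d3 | d12 | 12 × slope | Ratio to d12 | Slope power |
|---|---|---|---|---|
| 0 | -0.16 | -0.172 | 1.08 | 89% |
| -0.04 (linear) | -0.16 | -0.160 | 1.00 | 84% |
| -0.08 | -0.16 | -0.148 | 0.92 | 77% |
| -0.12 | -0.16 | -0.135 | 0.85 | 70% |
| -0.16 (plateau) | -0.16 | -0.123 | 0.77 | 62% |
| -0.16 | -0.08 | -0.037 | 0.46 | – |
| -0.16 | 0 | +0.049 | – | – |

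The 12-month change contrast has 81% power in every row with d12 = -0.16. In the plateau row, the slope test would need about 87 evaluable (97 randomised) per arm for 80% power.

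A simulation of the mixed model as written (300 runs per profile, 56 per arm) gave a mean 12 × slope of -0.165 with 85% power for the linear path, and -0.122 with 62% for the plateau.

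**4. Sensitivity to the meaning of 0.3.** The ratios above do not depend on the SD, but the power does. If 0.3 is a cross-sectional SD, the residual SD is 0.3 × √(1 - correlation). Power in the plateau case:

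| Within-child correlation | Slope | 12-month change contrast |
|---|---|---|
| 0.5 | 62% | 81% |
| 0.7 | 83% | 95% |
| 0.8 | 95% | 99% |

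**The case against.** Several points on the other side stand.

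- **A rate of change is a legitimate target.** The aim is worded as weight development, outcomes are taken at three visits, and only the sample-size statement names a 12-month difference. If there is no effect at either follow-up visit, the expected interaction is zero. The defect is misalignment between sizing and test, not an invalid test.
- **The trajectory is not documented.** A reader might infer from the session schedule that a plateau or fade is the most likely pattern. The protocol does not support that. It gives no 3-month effect, treatment continues through boosters to month 12, and the Background cites a recommendation that such programmes last at least six months. Contact hours are not BMI z-score change.
- **The power loss is not a single figure.** A reader might take 62% as the power of the planned test. It requires both a full plateau by month 3 and a particular reading of 0.3. At within-child correlations of 0.7 or 0.8, the slope test keeps more than 80% even under a plateau.
- **The sign reversal is easy to overread.** The +0.049 is an expected value when the true 12-month difference is zero. With an SE of about 0.0545, z is about 0.9, and significant apparent harm would occur in roughly 14% of such trials. The protocol gives no ground to expect a conclusion of harm.
- **The baseline weight-status term is not an error.** With complete data, a time-constant main effect leaves the slope contrast unchanged, and with 10% dropout simulated estimates moved only slightly. Including the stratification factor is harmless.

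Deferral to the SAP does not answer the core point, because the protocol already names both the parameter and its interpretation.

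**Conclusion.** The concern holds as a mismatch between the quantity sized and the quantity tested. The sample size arithmetic is correct for a 12-month difference. The primary parameter equals that difference only if the 3-month effect is one quarter of it. For a true 12-month difference of -0.16, the slope-implied value runs from -0.160 (linear) through -0.148 (half reached by month 3) to -0.123 (plateau, 23% too small), and an early effect that fades is distorted further.

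These ratios rest on complete data and on d0 = 0; missing visits would change the weights. The power consequence is conditional on both the trajectory and the meaning of 0.3. In the plateau case it ranges from 62% against 81% (SD of change, or cross-sectional with correlation 0.5) to 95% against 99% (cross-sectional with correlation 0.8). If the effect is truly linear there is no bias, and the slope is slightly more powerful.

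**What to change.** Before the SAP is finalised, specify the primary model with visit as a categorical factor (0, 3, 12 months), arm-by-visit terms and a common baseline mean across arms. Name the between-arm difference in BMI z-score at 12 months as the primary estimate and the 3-month difference as secondary. Keep the linear slope model as a sensitivity analysis. State whether 0.3 is the SD of the 12-month value or of the change. Carry the same visit structure into the analyses that reuse this model.

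The recruitment target stays at 126, because this contrast is what it was calculated for. If the effect is truly linear, the loss is about 3 points of power (81% against 84%, with 0.3 as the SD of change). The written model has five fixed parameters (intercept, arm, time, interaction, weight status); the core replacement has six (intercept, two visit terms, two arm-by-visit terms, weight status). Letting baseline weight status interact with visit would add two more, for eight in all. That is an optional refinement: it lets the stratification factor act on the change over time, which its main effect alone does not do with complete data.

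If a rate of change is what the investigators want to estimate, the alternative is to justify linearity and size the trial on the slope.

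### The dose-effect analysis swaps randomised arm for self-selected attendance, so its coefficient is not a causal effect of the number of ML sessions, and it conflicts with the blanket intention-to-treat statement

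*Protocol article*

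**What the plan says.** All of this is in the Data analysis section of the protocol article. It opens with "All analyses will be performed as an intention-to-treat analysis". The primary model is a linear mixed model with "BMI z-score at 0, 3, and 12 months as the outcome variable, including a random intercept for each child". On the right-hand side, "Fixed covariates will be treatment assignment (ML or control), time (in months), their interaction, and baseline weight status". For the primary result, "The effect of the treatment will be assessed by the interaction parameter".

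The section then adds: "A dose-effect analysis will be performed to assess the effect of number of ML sessions attended". The method, given in the next sentence, is "replacing the treatment variable in the regression model with a variable indicating how many sessions" the parents attended.

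Adjustment for confounding is stated for the comparison with the register controls ("using the same methods as described above adjusted for confounders") but not for the dose-effect analysis. No instrument, complier-type estimate or caveat about self-selected attendance is mentioned.

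**The concern.** The stated aim is causal, but the explanatory variable is not randomised. How many sessions a parent attends is decided after allocation and may depend on motivation, language, working hours or early progress, each of which may also bear on the child's weight. Once arm leaves the model, nothing protects the coefficient from these differences; the only other baseline term is weight status. The Discussion itself expects difficulty in keeping parents engaged, and reports the same from earlier ML studies, so attendance will vary between families.

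The analysis also cannot satisfy the section's own intention-to-treat rule, so one of the two statements has to give way.

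At stake is a statement that attending more sessions lowers BMI z-score, in a study meant to inform scale-up, when part or all of the association could come from who attends.

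**Working it through.** **Inputs from the protocol article.** Sample size: difference -0.16, SD 0.3, 80% power, alpha 0.05, 10% loss, 63 per arm. The Co-Fam model section: ten group and six booster sessions, so at most 16.

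**The plan's own figure.** n per arm = 2 × (1.96 + 0.8416)² × 0.3² / 0.16² = 55.2, so 56. Then 56 / 0.9 = 62.2, so 63 per arm and 126 in total. The stated size reproduces. About 57 per arm remain after 10% loss (63 × 0.9 = 56.7).

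**Assumptions not in the documents.** True ML effect zero; controls scored 0 sessions; attendance S in the ML arm with mean 10 and SD 4.5; correlation ρ between family motivation and 12-month improvement of 0.2 to 0.4; correlation r between motivation and attendance of 0.5, 0.73 or 1.0.

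**Bias in closed form.** The sessions variable s equals S in the ML arm and 0 in controls.

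- Var(s) = 0.5 × 4.5² + 0.25 × 10² = 10.1 + 25 = 35.1
- Cov(s, change) = -0.5 × ρ × r × 0.3 × 4.5
- Spurious effect at 16 sessions = 16 × Cov / Var

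For ρ = 0.3 and r = 1: Cov = -0.2025, slope = -0.2025 / 35.1 = -0.00577, times 16 = -0.09.

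**False-positive rates.** These come from simulation: 4,000 trials per setting, attendance capped at 0 to 16, change regressed on sessions, nominal 5%. Spurious effects are from the formula above.

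| r | Rate at ρ = 0.2 / 0.3 / 0.4 | Spurious effect at 16 sessions |
|---|---|---|
| 0.5 | 7 / 9 / 12% | -0.03 / -0.05 / -0.06 |
| 0.73 | 8 / 13 / 19% | -0.04 / -0.07 / -0.09 |
| 1.0 | 12 / 20 / 31% | -0.06 / -0.09 / -0.12 |

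At ρ = 0 the rate is 5%, so the excess comes from self-selection alone. The comparison by randomised arm stays at about 5% throughout.

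**Closer to the planned model.** Visits at 0, 3 and 12 months, with each child's slope regressed on sessions (r about 0.73, visit error SD 0.1), gave 8.4 / 15.5 / 23.1% for ρ = 0.2 / 0.3 / 0.4, and -0.07 at ρ = 0.3. These rates use the between-child variance of the slopes. The standard error of a random-intercept-only model is a separate matter and is left out here.

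**ML arm only.** Without controls the slope is -ρ × r × 0.3 / 4.5. At ρ = 0.3 and r = 0.73 this is -0.0146 per session, or -0.23 at 16 sessions. Simulation with capped attendance gave -0.25 and 36% false positives, against -0.06 and 13% with controls scored 0. Dropping the controls removes the randomised contrast and leaves only the self-selected one.

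**Arm as instrument.** The estimate is the arm difference divided by mean sessions. It averages 0.00 in these simulations, but by construction, because assignment acts only through sessions there. If assignment also shifted the outcome by an assumed +0.05 through other routes, the estimate at 16 sessions would be off by 0.05 / 10 × 16 = +0.08.

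**The case against.** The strongest reply is that this is a single supplementary sentence. It is not listed among the primary or secondary outcomes, it sits naturally beside dose received as a fidelity measure, and full details are deferred to an analysis plan that is not shown. That stands as a limit on importance. It does not make the point one of missing detail, because the article itself fixes both the causal aim and the method.

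Several stronger readings are tempting and not supported:

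- **That the plan scores controls as 0 and explains month-3 values by later booster sessions.** The text says neither. Zero for controls is the natural reading of replacing the treatment variable, but the count could be group sessions only or could accumulate by visit. Both faults are conditional.
- **That the error rate reaches about 31%.** This needs motivation to determine attendance completely, which is implausible if language and work also matter. At weaker links the rates are much lower.
- **That the bias must favour ML.** If families with greater need attend more, it would run the other way.
- **That the trial's main result is compromised, or that a null trial would be reported as a success.** The primary effect is the arm-by-time interaction, which is untouched. How the dose result would be reported is unknown.

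An instrument is not a clean cure either. The inclusion and exclusion criteria advise only intervention families against other structured treatment, so assignment can alter care by a route other than sessions. The Discussion also names spillover, since ML group leaders see families in both arms. With one binary instrument the estimate is the by-arm difference rescaled, so it cannot show whether more sessions do more.

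**Conclusion.** The point holds, as a fault in a supplementary analysis. As written, the dose-effect coefficient is not a causal effect of sessions attended, and the analysis contradicts the section's intention-to-treat sentence. Both follow from the text without any assumption about size.

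The size is assumption-bound. Under the null and the inputs above, false-positive rates run from about 7% to 31% and the spurious effect at full attendance from about -0.03 to -0.12, against a design difference of -0.16. The lower and middle parts of that range are the more credible. The plan should be changed, but the primary conclusion does not depend on it.

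**What to change.** 1. **For a causal statement,** estimate the per-session effect on 12-month BMI z-score, adjusted for baseline BMI z-score and weight status, by two-stage least squares with randomised arm as the instrument. Describe the result as a weighted average per-session effect. State that exclusion may fail because of the advice given only to ML families and because of spillover.
2. **If the attendance regression is kept,** label it exploratory and non-causal. Adjust it for baseline predictors of attendance that the parent questionnaire already collects, such as education, country of birth, years in Sweden and employment. Do not present a version restricted to the ML arm as a remedy, since it is more biased.
3. **Define the variable:** how controls are scored, which sessions count, and that only sessions held before each measurement are counted for it.
4. **Limit the intention-to-treat sentence** to the between-arm analyses.

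The cost is wording in the analysis plan, which the article says is still to be finalised, and no new data. The downside is precision and an explicit exclusion assumption. With the inputs above, the standard error at 16 sessions is 0.3 × √(2/57) × 16/10 = 0.090 for the instrument, against 0.3 / (√35.1 × √114) × 16 = 0.076 for the attendance regression, so the interval is roughly a fifth wider.
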